#### Participant Exclusion Criteria:

1. Unsuitable cognitive capacity as judged by the study physician;
2. Diagnosis of neurological injury other than SCI, such as stroke, traumatic brain injury; or other neurological condition that the study physician considers to be exclusionary;
3. Multiple spinal cord lesions;
4. History of frequent autonomic dysreflexia;
5. History of seizures;
6. Use of medications that significantly lower seizure threshold, such as anti-psychotics, tricyclic antidepressants, amphetamines, and bupropion;
7. History of implanted brain/spine/nerve stimulators, aneurysm clips, or cardiac pacemaker/defibrillator;
8. Deep vein thromboses in lower extremities of less than 6 months duration;
9. Pregnancy;
10. (Interventional phase only): Lack of detectable tibialis anterior MEP at baseline even with active facilitation;
11. (Interventional phase only): Inability to maintain supported upright posture without symptoms of orthostatic hypotension (light-headedness, pre-syncope);
12. (Interventional phase only): Active pressure ulcers greater than stage 1 severity on the foot, ankle, knee and/or pelvic girdle;
13. (Interventional phase only): Bone mineral density of the hip (proximal femur) T-score <3.5 SD from age- and gender-matched normative data;
14. (Interventional phase only): Any spasticity, contractures, or heterotopic ossification that result in inadequate range of motion of the shoulder, elbow, wrist, fingers, hip, knee, or ankle joints in the judgment of the study physician;
15. (Interventional phase only): Inability to cooperate with instructions or unwilling to commit to training sessions for three-four days per week over roughly 9 months;
16. (Interventional phase only): A diagnosis of coronary artery disease that precludes moderate to intense exercise.

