**Baseline testing (to be conducted over two visits):**

Once a participant has provided signed informed consent, a detailed review of the participant’s history and medical record will be conducted. A physical exam will be performed, including the Modified Ashworth Scale, the Spinal Cord Assessment Tool for Spasticity (SCATS) (Benz et al. 2005), and the American Spinal Injury Association (ASIA) Impairment Scale (AIS). Further clinical assessments will include the Berg Balance Scale; the Walking Index for Spinal Cord Injury II; the 10-meter walk test; the 10-second seated step test; a modified grasp-and-release test (Wuolle et al., 1994); pinch dynamometry; the Spinal Cord Injury Spasticity Evaluation Tool (SCI-SET) (Adams et al. 2007); the WHOQOL-BREF questionnaire (World Health Organization 1998); SCI-QoL questionnaire (Tulsky et al. 2011); and the

McGill Pain Questionnaire (short form). Depending on the severity of paraparesis, not all Participants will be able to perform the step or walk tests. As such, no baseline walking data will be collected for these outcomes in these participants. To ensure tolerance of upright position, heart rate and blood pressure will be measured for 10 minutes while the Participant is in an upright position supported using an overhead harness or standing frame. A full-body DXA scan will be performed. To be eligible for Phase 2 of the study, results from the DXA of the proximal femur must not have a T-score lower than 3.5SD below age/gender-matched controls. Seated and standing computerized posturography, motor evoked potentials, multiple tests of soleus H-reflex facilitation, and surface electromyography will also be assessed. At this point, the study evaluation is complete for participants with AIS A/B impairment. Only participants with AIS C/D injury or volitional strength of at least 1/5 in two or more key lower extremity muscles or some participants with electromyographic evidence for residual motor circuits will be eligible for the interventional component of our study. If any exclusion criteria are met, or if the participant decides at any time not to continue, he or she will not be further studied.

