**All participants will undergo baseline testing. Only participants with motor-incomplete SCI (AIS C/D grades or volitional strength of at least 1/5 in two or more key lower extremity muscles AND volitional strength of at least 3/5 in shoulder and elbow muscles) will participate in the exercise training phase as well as the post-training and follow-up assessment testing.**

The following procedures will be used:

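### Baseline testing schedules standing for every participant, but the pressure-ulcer and hip bone-density limits apply to Phase 2 only, so a Phase 1 participant known to meet either limit may still be stood

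*Protocol*

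**What the plan says.** Phase 1 admits AIS grades A to D (Participant Inclusion Criteria), and section 3a states: "All participants will undergo baseline testing".

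The Baseline testing section describes 10 minutes of heart-rate and blood-pressure monitoring "while the Participant is in an upright position supported using an overhead harness or standing frame". Its stated purpose is to confirm that the upright position is tolerated. The same section then lists "Seated and standing computerized posturography, motor evoked potentials" and further electrophysiology. Only after these does it say "At this point, the study evaluation is complete for participants with AIS A/B impairment". The Specific Aims also list standing posturography among the observational-phase assessments.

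Two limits bear on standing, and both are confined to Phase 2 in the exclusion criteria:
- Skin: "Interventional phase only): Active pressure ulcers greater than stage 1 severity on the foot, ankle, knee and/or pelvic girdle".
- Bone: "Interventional phase only): Bone mineral density of the hip (proximal femur"), with a cut-off of 3.5 SD.

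The second criteria list, in section 3a, labels both the same way. Baseline testing ties the scan to the later phase: "To be eligible for Phase 2 of the study, results from the DXA of the proximal femur" must not fall below the cut-off. Section 3b gives exclusion from the Interventional Phase as the only consequence of low density.

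**The concern.** Section 3b names skin breakdown and bone fractures among the risks of placing participants in a harness for upright sitting and standing. Its specific protection against fracture is the density exclusion, and its only stated action on a new ulcer of stage 2 or worse is to suspend training. Neither reaches someone who takes part in Phase 1 alone.

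Such a person may therefore be held upright and tested standing when the protocol's own limit is already known to be met. What is at stake is an avoidable exposure. The hold checks tolerance of standing, which is an inclusion criterion for Phase 2 and not for Phase 1. A participant who is currently barred from Phase 2 and can be tested seated has no stated need for it.

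**Working it through.** The protocol gives no figure to reproduce, so the check is a comparison of sections.

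1. **Who is stood?** Section 3a applies baseline testing to all participants. The upright hold carries no restriction by phase or AIS grade. Standing posturography comes before the point at which AIS A/B participants finish, and the Specific Aims list it for the observational phase.

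2. **Who is protected by the two limits?** Both criteria lists restrict the ulcer and density limits to the interventional phase. Baseline testing and section 3b do the same for density.

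3. **Does the general stop rule close the gap?** Baseline testing ends with "If any exclusion criteria are met, or if the participant decides at any time not to continue", after which the person is not studied further. For Phase 1 these two limits are not exclusion criteria, so the rule does not apply to them. Reading it more widely would contradict the phase labels.

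4. **Does the order of procedures close it?** Enrollment places a DXA scan and a physician's examination in screening, section 3b places the DXA before participation or enrolment, and Baseline testing mentions the DXA after the upright hold. No order is stated to be binding. The order is not decisive in any case: even an early DXA result has a stated consequence for Phase 2 only.

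5. **Do the other safeguards close it?** Section 3b provides a harness as needed, a mechanism limiting any fall to four inches, and at least two clinicians. These expressly cover assessments as well as training, but they are introduced to reduce falls. Fitting, padding and skin checks around each session reduce skin risk. None of these withholds standing from someone with an existing ulcer or low density.

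6. **How large is the exposure?** Phase 1 has one 10-minute hold plus any standing posturography, whose duration is not stated. Scheduled training in Phase 2 is 2 interventions × 48 sessions × 30 minutes = 2,880 minutes = 48 hours.

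7. **Is there a seated alternative?** Yes. The Computerized Posturography entry allows testing in either position, and item 12 of the secondary outcomes is based on seated Limits of Stability testing.

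**The case against.** The strongest reply is that this is a deliberate choice. The limits sit where the loading is, in 48 hours of training, and the risk sentence in section 3b speaks of therapy. The protocol gives no fracture or skin-injury rate for brief supported standing and does not show that the Phase 2 cut-off is the right bar for it. That much stands, and it keeps the point minor. It does not remove it, because Phase 1 itself includes dynamic posturography in standing, and section 3b treats standing assessments as needing protection.

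A second reply is that the hold may be meant as a Phase 2 screen, since standing tolerance and orthostatic symptoms are Phase 2 criteria. That reading is possible, but section 3a applies baseline testing to everyone and the text makes no such exception.

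A third reply is that staff would use judgement: the study physician attends most sessions and seated testing is permitted. This is plausible, but nothing links seated testing to ulcers or bone density.

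Two stronger readings are tempting and are not supported:
- A reader might infer that all AIS A/B participants will in practice be tested standing. The Berg Balance Scale entry expects most patients to be unable to do its standing items, and seated posturography is allowed, so many may be tested seated anyway.
- A reader might subtract the 24 Phase 2 participants from the 51 in Phase 1 and treat the remaining 27 as the most who could be affected. The ulcer criterion in the main list concerns active ulcers, which may heal before Phase 2, so someone affected at baseline could still be among the 24. Most reasons for not continuing also need have nothing to do with skin or bone.

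**Conclusion.** The gap is real and small. The protocol schedules an upright hold and standing posturography for all participants at baseline, confines the ulcer and hip-density limits to Phase 2, and gives no Phase 1 consequence when either is met. The conclusion rests on a literal reading of Baseline testing together with section 3a.

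The number affected is unknown, because the protocol gives no prevalence of ulcers above stage 1 or of hip density below the cut-off. The exposure is brief and supported. Power, the primary outcomes and the Phase 2 comparison are untouched. The protocol does not show that anyone would be harmed, and it would go too far to say that these people should be excluded from Phase 1. This is a cheap improvement in safety wording, not a flaw in the analysis.

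**What to change.** In Baseline testing:
- Require the skin examination (within the scheduled physical examination) and the DXA to be completed and read before the upright hold or any standing test. Align the DXA timing in Enrollment and section 3b with this.
- While a participant meets either existing limit, omit the hold, use seated posturography only, and record the reason, so that a test withheld for safety is not later read as inability to stand.
- If an ulcer heals and the participant is then considered for Phase 2, do the hold and the standing tests at that point, so that the Phase 2 baseline is complete.

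This adds no procedure and no new threshold, and removes nobody from Phase 1. Baseline already spans two visits, so the order should be workable.

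The cost is that some Phase 1 standing posturography will be missing, and missing selectively by ulcer status or bone density. In Phase 1 those data feed only the exploratory correlations and regression in Statistical Analysis. The seated Limits of Stability measure is kept for these participants. The loss cannot be sized from the protocol, and the write-up of those correlations should state how many standing tests were withheld and why.

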### **Randomization:**

Participants with motor incomplete SCI will receive the two training interventions in randomized order, with randomization occurring in blocks of 6 subjects.

#### **Berg Balance Scale: Sitting with Back Unsupported**

- 0** Unable to sit for at least 10 seconds
- 1** Able to sit 10 seconds
- 2** Able to sit 30 seconds
- 3** Able to sit 2 minutes under supervision
- 4** Able to sit safely and securely for 2 minutes

**Table 1** –Berg Balance Scale: Section on sitting with back unsupported.

### **Training period (48 sessions per intervention separated by a 6-week washout):**

Participants will undergo training with 30-minute sessions during 3-4 visits per week. Participants will have the option of performing up to two training sessions per visit to our center, with a break of at least 45 minutes between sessions. The two training paradigms will consist of 1) LOCOMOTOR training and 2) MULTIMODAL training. Training paradigms are described in detail in the next section.

### **Post-training evaluation:**

All the measures evaluated at the baseline visits will be repeated at the beginning and end of each training period. Evaluation will take place over one or two sessions within one week of the completion of each intervention.

### **6-Week Follow-up evaluation:**

All the measures evaluated at the baseline visits will be repeated at six weeks after completion of the second intervention.

### **Primary outcomes:**

1. Change from baseline in motor evoked potential amplitude in the tibialis anterior muscle; change from baseline in AIS lower extremity motor score.

### **Secondary outcomes:**

1. Change from baseline in AIS sensory scores.
2. Change from baseline in Berg Balance Scale score.
3. Change in leg spasticity on modified Ashworth Scale, Spinal Cord Assessment Tool for Spasticity, and Spinal Cord Injury Spasticity Evaluation Tool.
4. Change in gait speed on 10-meter Walk Test.
5. Change from baseline in Walking Index for Spinal Cord Injury II (WISCI II) scale.

6. Change from baseline in total number of steps taken by both feet during seated 10-second step test.
7. Change from baseline in total number of successful grasp-and-release trials taken by each hand (for cervical-level participants only).
8. Change from baseline in pinch dynamometry strength (in cervical-level participants only).
9. Change in quality of life as determined by WHOQOL-BREF and SCIQoL questionnaires.
10. Change in subjective pain as determined by McGill Pain Questionnaire (short form).
11. Change in percentage of upper and lower extremity lean tissue mass.
12. Change from baseline in endpoint excursion and directional control parameters achieved during seated Limits of Stability testing.
13. Change from baseline in soleus H-reflex facilitation and inhibition using appropriately timed physical stimuli, subthreshold transcranial magnetic stimulation, peroneal and tibial nerve stimulation.
14. Change from baseline in the Voluntary Response Index (VRI) for key leg muscles as detected by surface electromyography (Lee et al. 2004).

### **Research Design:**

This protocol will investigate the efficacy of combining fine-motor exercises with balance exercises in the rehabilitation of chronic thoracic spinal cord injury patients. There are two phases: an observational phase for participants with either motor complete or incomplete SCI; and an interventional phase for participants with motor incomplete SCI. The observational phase will characterize the residual function of specific neural circuits. The interventional phase will employ a single-group, single-blinded, pre-post-intervention crossover research design. We plan to enroll 51 participants for the observational phase. 24 participants with motor incomplete SCI will continue with the interventional phase, lasting approximately 9 months. The protocol will take 3 years to complete. We hypothesize that participants will demonstrate improved neural connectivity when undergoing multimodal training compared to locomotor training.

### **Statistical Analysis:**

For the observational phase, exploratory analyses will be undertaken to determine how well scores on the electrographic outcomes (evoked potentials, H-reflex testing, computerized posturography, surface electromyography) correlate with clinical outcomes such as gait disability, gait speed, and AIS motor and sensory scores. Using post hoc regression analysis, we hope to generate a preliminary model to predict anatomical and functional integrity of specific neural tracts based on performance on this battery of tests. This analysis and any resulting predictive model would need further validation with a prospectively studied population. The interventional phase of the study would not depend on the success of obtaining such a predictive model.

For the interventional phase of the study, participants will be randomly assigned to receive either locomotor training followed by multimodal training, or multimodal training followed by locomotor training. The primary outcomes will be change in tibialis anterior motor-evoked potential amplitude and change in lower extremity motor score (LEMS) compared to baseline. All other outcomes are secondary and exploratory.

The most rigorous method of analyzing data from crossover studies involves the use of independent-sample rather than paired-sample tests (Wellek & Blettner 2012). Therefore, outcome measures will be calculated within each subject as the percent change between baseline and completion of each intervention. The percent change across all subjects for each training modality will be compared using independent-sample t-tests or Mann-Whitney U tests depending on the normality of the data distribution. To test for the possibility that the washout period does not fully eliminate carryover effects, the percent change across all subjects for each training period (pre-washout, post-washout) will also be compared using independent sample tests. Statistical significance for all outcomes will be corrected for multiple comparisons using Bonferroni's method.

**Power Calculation:** Given that our training protocol is novel, we need to make predictions by extrapolating from other types of protocols. This is further hampered by the fact that most SCI

rehabilitation studies involve rather small numbers of participants in often inadequately controlled studies.

The most applicable study upon which to base our power analysis measured MEP amplitudes before and after 60-100 sessions of treadmill training in eight subjects with incomplete thoracic SCI (Thomas & Gorassini 2005). They found a  $46 \pm 12\%$  increase in maximal MEP amplitude post-training. Additionally, studies in uninjured volunteers demonstrated a 40-70% increase in MEP amplitudes with skilled training exercises but not passive movement or strength training (Jensen et al. 2005; Perez et al. 2004).

Due to these and other factors, we project an improvement of 50% with MULTIMODAL training versus 25% with TREADMILL training. The use of a crossover design will reduce inter-subject variability between the two training modalities compared to a parallel-group design. We conservatively project an estimated variance of 25% for each group – this magnitude of variance is larger than the average variance seen in the MEP studies cited above. Based on these numbers, the calculated power to detect a difference between the two training groups on a two-tailed independent-sample *t*-test or Mann-Whitney test is greater than 80% with 18 subjects, at an  $\alpha = 0.05$ . We will enroll 24 subjects to account for up to a 25% dropout rate.

|                | Year 1 | Year 2 | Year 3 | Total N |
|----------------|--------|--------|--------|---------|
| Phase 1 | 15     | 18     | 18     | 51      |
| Phase 2 | 6      | 10     | 8      | 24      |

**Table 3** Clinical Study Timeline – Participants enrolled per year.

**3a. Basic Information** (Even if described under “Procedures”, list the information requested below where pertinent.)

The study will occur in two phases: An observational phase, in which participants will undergo a series of clinical and neurophysiological tests; and an interventional phase, in which participants with incomplete SCI will undergo standard LOCOMOTOR training and experimental MULTIMODAL training in random order. Training will continue for 48 sessions per intervention, separated by a 6-week washout period. The clinical and neurophysiological tests will be repeated at the end of each intervention.

**All participants will undergo baseline testing. Only participants with motor-incomplete SCI (AIS C/D grades or volitional strength of at least 1/5 in two or more key lower extremity muscles AND volitional strength of at least 3/5 in shoulder and elbow muscles) will participate in the exercise training phase as well as the post-training and follow-up assessment testing.**

The following procedures will be used:

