## 2. BRIEF REVIEW OF RESULTS OF OTHERS AND CURRENT STATE OF KNOWLEDGE

### The spared fibers of spinal cord injury

Traumatic spinal cord injury (SCI) only rarely leads to complete cord transection – most injuries occur through external trauma to the spinal column, leading to varying degrees of cord contusion (NSCISC 2013). Therefore, rather than severing the cord, most injuries leave a portion of the cord's nervous tissue intact (Hayes & Kakulas 1997; Kakulas 1987). Even in patients who cannot consciously sense or move their body below a lesion, there is often some degree of motor, sensory, and/or autonomic circuit sparing (McKay et al. 2004; Sherwood et al. 1992).

[figure not shown]

**Figure 1** – Schematic of corticospinal (red) and brainstem tracts (green) after anatomically incomplete cervical spinal cord injury (A). Note that only brainstem fibers survive below the lesion. Repetitive simultaneous firing of CST and brainstem tracts (B-C) leads to strengthening of alternative connections between CST fibers and brainstem neurons. In this fashion, a detour pathway reforms between the cortex and motor neurons on the previously denervated side of the cord (D).

Spared circuits represent a potential pathway for recovery – therefore, it is crucial to characterize their identity in individual patients. Due to their anatomically diffuse distribution, fibers of brainstem and spinal tracts (for example, the reticulospinal tract) are much more likely to survive cord damage than those of cortically-originating tracts such as the corticospinal tract (CST) (Jankowska & Edgley 2006; Nathan et al. 1996).

If we were better able to detect and characterize spared neural pathways, clinicians could give patients not only a more accurate prognosis, but perhaps better treatment – that is, interventions more specifically targeted toward spared circuits could improve rehabilitation outcomes. This proposal presents the rationale, preliminary data, and research design intended to achieve these goals.

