### 3. PROCEDURES, METHODS AND EXPERIMENTAL DESIGN.

#### Participant Inclusion Criteria:

##### Phase 1 Functional and electrophysiological assessment of residual circuitry

1. Age between 21 and 65 years;
2. Chronic thoracic SCI (levels C2-T12; more than 12 months since injury);
3. AIS grades A, B, C, or D.

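### Phase 1 correlations across AIS A–D can, for floor-prone pairs such as tibialis anterior MEP with leg motor score, reflect the complete/incomplete split alone; add within-group results

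*Protocol*

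**What the plan says.** The Phase 1 inclusion criteria admit "AIS grades A, B, C, or D", and Research Design describes "an observational phase for participants with either motor complete or incomplete SCI". The sizes are given there too: "We plan to enroll 51 participants for the observational phase" and "24 participants with motor incomplete SCI will continue with the interventional phase".

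Under Statistical Analysis the protocol states that "exploratory analyses will be undertaken to determine how well scores on the electrographic outcomes" agree with the clinical picture. The tests meant are evoked potentials, H-reflexes, posturography and surface EMG, and the task set for them is to "correlate with clinical outcomes such as gait disability, gait speed, and AIS motor and sensory scores". The next step is a regression on the test battery: "Using post hoc regression analysis, we hope to generate a preliminary model" of the integrity of specific neural tracts. The section gives no analysis within motor-complete or motor-incomplete participants and does not mention AIS grade as a covariate. It does say that any model would need validation in a prospectively studied population, and that the interventional phase does not depend on it.

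The background section explains why the tests are of interest: "Even in patients who cannot consciously sense or move their body below a lesion, there is often some degree of motor, sensory, and/or autonomic circuit" (cut off one word short; the missing word says that these circuits are spared).

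**The concern.** The case for the battery is that it may show spared circuits that the clinical examination does not. A correlation taken over AIS A to D answers a different question, namely whether the tests and the examination both separate severe from less severe injury. If motor-complete participants cluster at the bottom of both scales, that cluster alone produces a correlation, even when the test says nothing about differences among motor-incomplete people. AIS motor score adds some circularity as a correlate, because AIS grade is partly built on it.

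The opposite case is also awkward. A motor-complete participant with a recordable MEP is the finding the background section hopes for, yet that participant would lower the overall correlation.

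At stake is the reading of the only analysis given for the observational aim. A grade-driven coefficient could be taken as evidence that the battery identifies spared circuits. A later cohort with the same A-to-D mix would reproduce that coefficient, so prospective validation alone would not expose the problem.

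**Working it through.** The protocol gives no target correlation, precision or power for Phase 1, so there is no stated figure to reproduce. The check asks how large an overall correlation the split alone can create.

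**Inputs from the protocol**
- N = 51, AIS A to D (Research Design; inclusion criteria).
- 24 motor-incomplete participants go on to Phase 2, so at most 51 − 24 = 27 are motor complete. The true number is not stated. Phase 2 has further entry conditions, so some motor-incomplete people may be in Phase 1 only. Assumed range: 13 to 27.
- Absent tibialis anterior MEPs are foreseen (H-reflex facilitation procedure), so an MEP floor is possible.
- WISCI II runs from 0 to 20 (Clinical Tests), so a floor is possible there too.

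**Assumptions (the protocol gives no figures)**
- In motor-incomplete participants, MEP has mean 1 and SD 0.8 (ratio k₁ = 1.25), leg motor score has mean 28 and SD 12 (ratio k₂ = 2.33), and the two are independent.
- All motor-complete participants score zero on the clinical measure. A share f of them have zero MEP; the rest have MEPs distributed as in the motor-incomplete group.

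**Formula.** With q the motor-complete share of the 51,

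r = (1−q)·q·f·k₁·k₂ / √[(1−q)(1+q·k₂²)(1−q·f)(1+q·f·k₁²)].

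For f = 1 this reduces to q·k₁·k₂ / √[(1+q·k₁²)(1+q·k₂²)]. With q = 27/51 = 0.529 it gives 1.544 / √(1.827 × 3.882) = 0.58.

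| Motor complete | f = 0 | f = 0.25 | f = 0.50 | f = 0.75 | f = 1 |
|---|---|---|---|---|---|
| 13 of 51 | 0 | 0.10 | 0.20 | 0.30 | 0.41 |
| 20 of 51 | 0 | 0.12 | 0.25 | 0.37 | 0.51 |
| 27 of 51 | 0 | 0.13 | 0.26 | 0.41 | 0.58 |

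**Simulation check** (gamma-distributed scores, N = 51, 4,000 runs per cell). Mean r agrees with the formula to within about 0.02. The overall correlation is significant at two-sided 0.05 in:
- f = 1: 93% of runs (13 motor complete) to 100% (27);
- f = 0.75: 63% to 88%;
- f = 0.50: 32% to 51%;
- f = 0: 5%.

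Restricted to motor-incomplete participants, the rate is about 5% throughout.

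**Sensitivity to spread.** With equal ratios k for both measures and f = 1, r = q·k²/(1+q·k²). For k = 1, 1.5 and 2 this gives 0.20, 0.36 and 0.51 with 13 motor complete, and 0.35, 0.54 and 0.68 with 27. Ranks do not remove the effect: mean Spearman is about 0.58, 0.76 and 0.88 with 13, 20 and 27 at the floor on both.

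**Adjusting for motor status alone.** With f = 1, a partial correlation adjusted for a complete/incomplete indicator still rejects in 9% to 19% of simulations with no true association, because one group has no variation.

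**Price of restriction.** The smallest significant |r| is t/√(df + t²). At n = 51 it is 2.010/√(49 + 2.010²) = 0.28; at n = 24 it is 2.074/√(22 + 2.074²) = 0.40.

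**Regression fit.** As an illustration only, the test descriptions yield about 22 candidate measures for one leg: MEP 3 muscles × 3 measures = 9, H-reflex 8, seated stability 2, EMG 3. If all 22 were entered and were pure noise, expected apparent R² would be 22/50 = 44%. The protocol fixes no predictor set, so this shows why apparent fit is a poor summary here; it does not forecast the result.

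**The case against.** The strongest reply is that the protocol promises little. It calls the analyses exploratory and the model preliminary, asks for prospective validation, and keeps the interventional phase independent of the result. It never says that the groups will be pooled, and stratification or covariates may be left to a statistical analysis plan. Agreement with clinical scores across the whole severity range is also a legitimate question, and a real difference between complete and incomplete injury is part of its answer. All of this stands and limits the point to an improvement. It does not change what the stated correlation measures.

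A reader might infer that motor-complete participants sit at the floor on every pair, so that strong correlations are bound to appear. The protocol does not support that:
- Step and walk test data are not collected from people who cannot do the tests (Baseline testing), and the 10-meter walk is for ambulatory participants only. Gait speed is therefore missing in them, not zero.
- Motor completeness does not put sensory scores at a floor. Hand-muscle MEP, basic H-reflex measures and seated posturography are not shown to have one.
- The background section expects sparing in some clinically complete injuries, so a uniform MEP floor cannot be assumed.
- Phase 2 entry by leg strength or EMG evidence, as an alternative to AIS C or D, implies that some participants outside those grades are not at the floor.
- 27 of 51 is an upper bound on the motor-complete share.

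A reader might also infer that only an apparent fit will be reported for the model. The protocol does not say so; it specifies no fit statistic.

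**Conclusion.** The point holds for floor-prone pairs only, chiefly tibialis anterior MEP with leg motor score or WISCI II. For these, the complete/incomplete split alone can give r of about 0.4 to 0.6 if all motor-complete participants are at the floor on both measures, about 0.2 to 0.4 if 50–75% of them lack an MEP, and nothing if none do. These figures rest on assumed means and SDs and on 13 to 27 motor-complete participants. With other spreads, the full-floor range widens to 0.20–0.68. That a strong correlation must appear is not established. The weakness is one of interpretation, and it is worth correcting because it concerns the sparing that the observational aim is meant to describe.

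**What to change.** Amend the observational paragraph of Statistical Analysis as follows:

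1. Keep the overall correlation, and beside it report each correlation within motor-incomplete participants, and within motor-complete participants where the clinical score varies.
2. Describe electrophysiological sparing separately in the motor-complete group, for example the number with a recordable tibialis anterior MEP.
3. Fit the preliminary regression with AIS motor status included, use a penalised fit, and report bootstrap- or cross-validated performance.
4. Do not make the motor-status-adjusted partial correlation the headline result, given its 9–19% false rejection when one group is fixed at zero.

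This changes analysis wording only and needs no new visits or data. The cost is precision: intervals within groups are wider, and the smallest significant |r| rises from about 0.28 at n = 51 to about 0.40 at n = 24. The within-group coefficients may also look less impressive.
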